## Abstract

**Background:**

Immunization programs are among the most effective public health strategies worldwide. Adequate vaccine storage is a prerequisite to assure the vaccines’ effectiveness and safety. In a questionnaire survey among a random sample of German primary care physicians, we discovered vaccine storage deficits: 16 % of physicians had experience with cold chain breaches either as an error or near error, 49 % did not keep a temperature log, and 21 % did not use a separate refrigerator for vaccine storage. In a recent feasibility study of 21 practice refrigerators, we showed that these were outside the target range 10.2 % of the total time with some single refrigerators being outside the target range as much as 66.3 % of the time. These cooling-chain deficits are consistent with the international medical literature, yet an effective, easy to disseminate, practice-centered intervention to improve storage conditions is lacking.

**Methods/design:**

This randomized intervention trial will be conducted in a random sample of primary care practices. Based on continuous temperature recordings over 7 days, all practices with readings outside the target range for vaccine storage (+2 °C to +8 °C) will be randomly allocated to a web-based education program or a waiting list control group. The practice physicians and their teams constitute the target population. Participants will be educated about best practices in vaccine storage and will receive a manual including storage checklists and templates for temperature documentation. In all practices, temperatures of the vaccine refrigerators will be monitored continuously using a data logger with a glycol probe as a surrogate for vaccine vial temperature. The effectiveness of the web-based education program will be determined after 6 months in terms of the proportion of refrigerators with vaccine vial temperatures within the target range (+2 °C to +8 °C) during 7-day temperature logging. Secondary outcome parameters include temperature monitoring, no critically low temperatures (≤ -0.5 °C), compliance with storage recommendations, knowledge of good vaccine storage conditions, and assignment of personnel as vaccine storage manager and backup.

**Discussion:**

Keep Cool will develop and evaluate a web-based education program to improve vaccine storage conditions in primary care and thereby ensure immunization safety and effectiveness.

**Trial registration:**

DRKS00006561 (date of registration: 20 February 2015)

## Background

Immunizations are among the most effective and cost-effective public health strategies worldwide [1]. Adequate vaccine storage is a prerequisite to maintain effectiveness and safety of the vaccines. The maintenance of the vaccine cold chain (2 °C to 8 °C) is of utmost importance to assure vaccine potency [2]. Detailed analyses of vaccine temperature sensitivities documented freezing of vaccines as being more critical than heating, at least in our moderate Western European climate. Modern adsorbed hepatitis B vaccines were documented to be the most sensitive vaccines with a freezing point of -0.5 °C [2]. At this temperature, irreversible precipitates of aluminum-containing adsorbents begin to form, which decrease the potency and can induce local irritation upon injection [2, 3].

In a cross-sectional web-based questionnaire survey, we analyzed vaccination management among a 10 % random sample of primary care physicians from one of Germany’s largest federal states, North Rhine-Westphalia [4] using international recommendations for vaccine storage [5–9]. The survey (n = 211) revealed that 16 % of the primary care physicians have experience with cold chain breaches either as an error or near error; 8 % do not regularly control their storage with regard to vaccine wrapping, vaccine expiration date, and refrigerator temperature; 49 % do not keep a storage temperature log; and 21 % fail to use a separate refrigerator solely for vaccine storage. In a recent feasibility study, we observed that the correct temperature range of 2 to 8 °C was not consistently maintained in seven of 21 (33.3 %) vaccine refrigerators from teaching practices. Refrigerators were outside the target range 10.2 % of the total time, with single refrigerators outside the target range for as much as 66.3 % of the time. These results are in line with studies worldwide, which discuss the following key problems related to vaccine storage: 1) temperatures outside the target range [10, 11], 2) lack of adequate temperature measurement devices [12–14], 3) lack of continuous temperature documentation [4, 12–14], 4) use of inadequate refrigerators [9, 10, 12], 5) lack of separate refrigerators [13–15], 6) inadequate storage practices [2, 12, 14, 15], 7) lack of designated personnel [14], and 8) insufficient staff training and guidance [12, 14, 16–18].

Prior studies addressing these deficits used the following intervention components either alone or in combination: 1) written educational materials, 2) introduction of thermometers with or without feedback on temperature readings by either graphic display or telephone advice to personnel, and 3) 1:1 onsite education with inspection of refrigerators. In 2002, a prospective intervention study of 721 US primary care practices achieved improved compliance with several storage recommendations of up to 19 % after 3 months following the distribution of a manual, a thermometer and a feedback checklist [12]. Similar results with improvements ranging from 13 to 23 % after 4 weeks were shown in a Korean study of 39 private clinics, which provided onsite 1:1 education including the distribution of a manual. This study also documented improved awareness of various vaccine storage criteria ranging from 3 % to 29 % [16]. With regard to reaching the targeted temperature range, the best result was observed in an Australian study of 50 primary care practices: onsite education and the distribution of min/max-thermometers led to a fourfold increase of practices with refrigerator temperatures in the target range [18]. The two studies available, which provided long-term follow-ups after 6 months, 1 year, and 5 years, documented a tendency for improved temperatures in the populations studied but also reported fluctuations over time in 25 % of the practices with initially optimal temperatures [19, 20]. The repetitive documentation of such fluctuations in intervention as well as control groups underlines the need for structural change as part of educational interventions, including the long-term implementation of practice routines for daily temperature monitoring.

Following recommendations on effectively changing medical practice [21], our study will use a complex approach focusing on the individual as well as the organizational level by encouraging structural changes. The intervention will address both professional groups involved in the management of vaccines, that is, the physician managers in charge, as well as the practice assistants who handle vaccines. Based on didactic approaches such as information tailoring and confidence-based learning, relevant information will be presented in a web-based education program, which tailors information to each users’ knowledge. Prospectively, this e-learning approach will allow for widespread dissemination at low cost.

Keep Cool aims to evaluate the effectiveness of a web-based education program to improve vaccine storage conditions in primary care practices. The main outcome used to determine the effectiveness of the intervention is the proportion of refrigerators with vaccine vials within the target range (+2 °C to +8 °C) during 7-day monitoring after 6 months.

## Methods/design

### Study design

Keep Cool is a prospective, randomized, controlled intervention trial, which will be performed in a random sample of primary care practices (see Fig. 1). After telephone recruitment, all practices will be visited by a study assistant to set up temperature data loggers (t0). Based on continuous temperature recordings over 7 days, all practices with readings outside the target range for vaccine storage (+2 °C to +8 °C) will be randomly allocated (1:1) to an intervention group or a waiting list control group. Practices with temperatures within the target range will be followed separately to monitor temperature fluctuations. Baseline data on knowledge will be collected at t1 prior to the start of the intervention, whereas the compliance with storage recommendations and the assignment of personnel as vaccine storage manager and backup will have already been documented by the study assistant during recruitment (t0). After baseline measurements at t1, the intervention group will receive access to the e-learning program. Follow-up data will be obtained after 6 months (t2) and, to study the intervention’s long-term effectiveness, after 1 year (t3) and 18 months (t4). After the intervention phase is completed, the waiting list control group will receive access to the e-learning program.

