### Outcomes

*Primary outcome:* The proportion of refrigerators with vaccine vials within the target range (+2 °C to +8 °C) during a 7-day monitoring at 5-minute intervals after 6 months. Temperature inside the target range is chosen as the primary outcome, because it is of utmost importance that nonfreezing vaccines are stored in this temperature range. When absorbed mono- and combination vaccines reach their individual freezing thresholds, their chemical structures irreversibly change. This can lead to increased local reactions and reduced effectiveness. The most sensitive vaccines are hepatitis B vaccines with a freezing threshold of -0.5 °C [2]. A thermal analysis of frequently used types of refrigerators by the US Department of Commerce [22, 23] showed that vaccine vial temperatures vary depending on the refrigerator type, loading density and location of vaccines inside the refrigerator. Typical refrigerators used in German primary care are the types “freezerless” (single refrigerator compartment without a freezer) and “dual zone” (separate compartments for refrigerator and freezer, both with individual doors), both so-called domestic refrigerators. Based on different scenarios, that is, door openings and loading density, temperatures can vary by +/-2.3 °C in the type “freezerless” and by +/-4.5 °C in the type “dual zone” [22, 23]. The maintenance of the temperature range of +2 to +8 °C, as recommended by vaccine manufacturers and public health authorities worldwide, is hence justified and therefore serves as a primary outcome measure.

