##### Waiting list control group

The control group will consist of practices that have temperature readings outside the target range during baseline data collection. The control group will be monitored via a temperature data logger but will receive access to the e-learning program only after t2. By including a control group, an intervention bias due to the set-up of data loggers is taken into account. The control group is closest to regular everyday care and serves as a baseline to better determine the effectiveness of the intervention.

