### Safety issues

All practices will be informed in detail about their vaccine refrigerator temperature. The tailored education and the download material will address the issue of how to deal with temperature breaches. Practices with temperature readings outside the target range will receive additional information after t2. The following safety regulations will be followed:Practices with any temperature beyond the target range will receive detailed information on the date and duration of the incident.They will also receive detailed information recommending that the manufacturer’s hotline(s) be contacted for information on how to deal with vaccines exposed to inadequate temperatures, and if additional vaccinations of patients are required to assure patient immunity.In addition, practices will receive the contact data of the Paul Ehrlich Institute, the Federal German agency responsible for vaccines and appropriate management thereof.

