### Statistical analysis

Descriptive statistics will be used to describe baseline characteristics for both study arms with regard to practice characteristics (single/group, number of physicians/medical assistants in practice, number of patients quarterly, average number of vaccinations daily/per week, age structure of patients), participating physician and practice personnel characteristics (sex, age, years in practice/job, part-time/full-time, job content). The effectiveness will be assessed by comparing the intervention and control group and by intragroup comparison (baseline versus follow-up). We will evaluate the effectiveness based on temperature as the main outcome (within range yes/no) by comparing both groups using the chi-square test. For intergroup analyses, all dichotomous secondary outcomes will be evaluated using chi-square tests for each item. In addition, compliance with storage recommendations will be analyzed on the basis of a sum score calculated across all items by using a t-test. For in-group comparisons, McNemar tests will be calculated for dichotomous outcomes and t-tests for dependent samples for sum scores. Temperature monitoring will be measured on an ordinal level to allow for application of the Mann-Whitney U Test (intergroup comparison) and the Wilcoxon signed rank sum test (intragroup comparison). A *P* value <0.05 will be considered significant. All statistical analyses will be performed using IBM SPSS 22® on Windows.

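### Unless control access waits until after t4, no untrained randomised arm remains at t3 and t4, so the stated comparisons cannot show long-term effectiveness

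*Protocol article*

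**What the plan says.** All references are to the Protocol article.

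- **Purpose of the late visits.** Study design sets t3 and t4 to study the intervention's "long-term effectiveness, after 1 year (t3) and 18 months (t4".
- **When controls are trained.** Under Waiting list control group, the control group "will receive access to the e-learning program only after t2". Study design words it differently: "After the intervention phase is completed, the waiting list control group will receive access to the e-learning program". That sentence names no visit.
- **Other input after t2.** Safety issues adds: "Practices with temperature readings outside the target range will receive additional information after t2". It makes no distinction by arm.
- **Analysis.** Statistical analysis states: "The effectiveness will be assessed by comparing the intervention and control group and by intragroup comparison (baseline versus follow-up". It names a chi-square test between arms and McNemar tests within arms, and ties neither to a visit.
- **Primary time point.** Outcomes fixes the primary outcome "during a 7-day monitoring at 5-minute intervals after 6 months", which is t2.
- **Other cohort.** Study design says: "Practices with temperatures within the target range will be followed separately to monitor temperature fluctuations". These practices are not randomised.

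**The concern.** A claim of long-term effectiveness needs a reference group without the program at the long-term visits. If controls gain access soon after t2, the randomised contrast at 12 and 18 months is early against late access. A lasting benefit in both arms then shrinks the difference, and a reader could take that as loss of effect. The change from baseline errs the other way, because practices enrolled for being out of range can only stay as they were or improve on the primary outcome.

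Durability matters to this trial. The Background reports fluctuations in 25 % of practices with initially optimal temperatures and uses them to argue for structural change. Secondary outcomes are touched too: the storage checklist is repeated at t3 and t4, and the knowledge questionnaire and logbook inspection at t4.

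**Working it through.** **Inputs.** From Sample size estimation: 70 % of intervention and 30 % of control practices in range at follow-up, 23 practices per arm, 80 % power, 20 % dropout. The significance level is 0.05 as in Statistical analysis, taken as two-sided. The sample size section prints 0.05 %; a literal 0.0005 would need 57 per arm, so 0.05 is meant.

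**Step 1: reproduce the plan's figure.** With mean proportion 0.5,

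n = [1.96·√(2·0.5·0.5) + 0.842·√(0.7·0.3 + 0.3·0.7)]² / 0.40² = (1.386 + 0.545)² / 0.16 ≈ 23.3, which rounds up to 24.

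The arcsine formula gives 23.2. With 23 per arm, power is 0.79 by normal approximation and 0.81 by exact enumeration of the uncorrected chi-square test. The stated 23 per arm and 80 % are therefore reproduced. Dropout: 46 / 0.8 = 57.5, so 58, as stated.

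**Step 2: the between-arm test at t3 or t4.** Keep 23 per arm and let intervention practices hold at 70 %. The protocol gives no rate for controls after late training, so a range is assumed. Power is the exact rejection probability of the uncorrected chi-square test.

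| Control rate in range | Difference (points) | Power |
|---|---|---|
| 30 % (untrained, as at t2) | 40 | 0.81 |
| 50 % (assumed) | 20 | 0.29 |
| 60 % (assumed) | 10 | 0.11 |
| 70 % (assumed, same response) | 0 | 0.05 |

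If the early arm instead wanes to 50 % while newly trained controls reach 70 % (also assumed), the difference is 50 − 70 = −20 points. By symmetry with the second row, the chance of a significant result is again 0.29, now against the intervention arm.

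**Step 3: the within-arm test against baseline.** Every randomised practice is out of range at t0, so all discordant pairs point towards improvement. With k practices converting, the exact two-sided McNemar p-value is 2·0.5^k:

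- k = 5: p = 0.0625
- k = 6: p = 0.031
- k = 7: p = 0.016

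Six conversions are enough for significance. At the protocol's 30 % rate without training, the expected number is 0.30·23 = 6.9, and P(X ≥ 6) for a binomial with n = 23 and probability 0.30 is 0.73. An untrained group would thus usually show a significant improvement. The control group is there to account for this monitoring effect, and after t2 it no longer can.

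**The case against.** The strongest reply has four parts.

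1. **The statistical section assigns no test to t3 or t4.** An article may leave that to a fuller document. This stands in part: a reader might infer that a between-arm test is definitely planned at the late visits and that a lasting benefit will appear as a vanished effect. The text does not say so, and the planned change from baseline would not vanish. What remains is that effectiveness is the stated purpose of t3 and t4, the comparisons are not limited to t2, and neither has an untrained reference later. A fuller analysis plan could relabel the analyses but could not restore an untrained arm.

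2. **The date of control access is not fixed.** After t2 is only an earliest time, the wording in Study design is looser, and the study overview figure is not available here. If access came after t4, the problem would not arise. Soon after t2 is the likelier reading, but the conclusion must carry that condition.

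3. **The early-versus-late contrast is not blind to durability.** This is right. A reader might infer that the expected difference is zero whatever happens to the effect. Zero requires equal rates in both arms; waning in the early arm alone gives a negative difference. The contrast mixes durability with the controls' own response, so it cannot isolate either.

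4. **Season.** A reader might add season as a reason to distrust the change from baseline. The 1-year visit falls at about the same time of year as baseline, so this does not apply to t3. It could apply at 18 months, but the documents do not discuss it.

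A waiting list is also a normal and defensible trade-off. Nothing here asks for training to be withheld.

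**Conclusion.** The point holds, on the condition that controls gain access before t3 or t4. Neither planned comparison can then answer the long-term question. The between-arm difference falls from 40 points (power 0.81) to between 20 and 0 points (power 0.29 to 0.05) when the early arm holds at 70 % and late-trained controls reach 50 to 70 %, and it can change sign if the early arm wanes. The baseline comparison would favour even an untrained arm about 73 % of the time.

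These figures rest on the protocol's 70 % and 30 %, on 23 practices per arm still being measured at t3 and t4, and on assumed control rates after training.

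A reader might infer that the trial's main result is compromised. It is not: the primary comparison at t2 precedes control access, and its sample size reproduces. The defect is confined to the long-term claim.

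**What to change.** - Reconcile Study design with Waiting list control group so that both name the same visit for control access.
- State that t2 is the only controlled comparison of effectiveness.
- Relabel t3 and t4 as descriptive follow-up by time since program access, without between-arm effectiveness tests.
- Report the proportion in range with a confidence interval at t2, t3 and t4 among all intervention practices.
- Add maintenance among intervention practices in range at t2 as a supplement only. This subset is selected on the outcome, so regression to the mean will look like decay, and it is small: 70 % of 23 is about 16 practices, and 12 of 16 maintained would have a 95 % Wilson interval of about 51 to 90 %.
- Show the non-randomised in-range cohort as a descriptive benchmark for fluctuation, and the control arm's t2-to-t3 change as an uncontrolled replication.

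The cost is some rewording and a short re-specification of the late analyses, with no extra data collection. The price is a more modest long-term claim.

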**Fig. 1 Fig1:**
[figure not shown]
Study overview

Ethical approval was obtained from the Ethic Commission of the Medical Faculty of the University Hospital Essen, University of Duisburg-Essen (reference number: 14-6118-BO, date of approval: 04/02/2015). Keep Cool follows the Ethical Principles of the World Medical Association Declaration of Helsinki (WMA 1964).

### Study population

The target population of this randomized controlled trial is primary care physicians and their practice personnel. The majority of these personnel completed a 3-year vocational training with a degree (practice assistants). A few practices also employ secretaries, nurses or personnel without a degree, but with on-the-job training. The intervention will address all staff members handling vaccines regardless of their prior training. Practices are eligible if they administer vaccinations and are situated within a 50-km radius of Essen, Germany. All participating physicians and practice personnel will sign an informed consent form.

### Intervention: web-based education program

Physicians and practice personnel will participate in a web-based education program on the storage of vaccines according to international best practices (for example, WHO and CDC). To ensure the target populations’ acceptance of the program, we will ask primary care physicians and practice assistants of academic teaching practices of our research network to join recurrent focus group sessions. This group will facilitate the development, adaptation, implementation, and evaluation phase of the intervention.

The e-learning program will be developed using a teaching software that allows the tailoring of information to each user group (that is, physicians and medical assistants) and each individual’s previous response behavior. Following confidence-based learning, the e-learning program will require participants to a) answer concrete vaccine storage-related questions and b) indicate the degree to which they feel confident in the correctness of each answer. Depending on the respondents’ answers, that is, correctness and confidence of answers, each participant will receive learning input with subsequent learning-success-adjusted repetitions of questions to achieve optimal memorizing effects. All participants will receive tailored feedback during the course of answering questions on an item level and for all items after completion of the program.

Five educational topics will be addressed by the web-based education program:Requirements for technical equipment including refrigerator criteria; types of thermometers; equipment maintenance.Vaccine temperature sensitivity, target temperature, and daily reviewing and recording of temperatures: freezing thresholds of freeze-sensitive vaccines; refrigerator target range (2-8 °C = 35.6-46.4 °F); necessity of daily recording; recording criteria; need for long-term temperature logs; and use of data logs (paper-based or electronically).Principles of vaccine storage inside a refrigerator including the preparation of refrigerators for vaccine storage, background knowledge about the use of domestic refrigerators for vaccine storage (incl. refrigerator cycles, temperature zones), necessity of a separate refrigerator for the sole purpose of vaccine storage, standards for vaccine storage within refrigerators, and use of storage aids.Vaccine cold chain-related processes including vaccine arrival procedures, periodic manual storage control, and procedures for dealing with cold chain breaches and equipment failure.Responsibilities of practice personnel including the assignment of personnel as vaccine storage manager and backup.

To facilitate long-term changes at the organizational level, all practices will be advised to assure the following two structural components: 1) the assignment of personnel as vaccine storage manager and at least one backup and 2) the set-up of a comprehensive temperature monitoring system. This includes reviewing temperatures using a standard thermometer, recording temperatures in a temperature log, taking immediate action if needed, and retaining temperature logs. In addition to a storage manual summarizing the program content, the following material will be made available as a web download: a “temperature log template,” guides for “preparing a refrigerator for vaccine storage,” “storing vaccines in the refrigerator,” “refrigerator maintenance,” plans for “routine vaccine management,” and “emergency response,” as well as a summarizing overview of the “tasks of the vaccine coordinator.”

